#### Control group

2.6.2

Participants assigned to the CG will be required to undertake aerobic activity by performing a minimum of 10,000 steps per day to meet the physical activity guidelines but will not be involved in supervised resistance training. We thus aim to guarantee that all enrolled participants benefit from being physically active as they are all required to comply with aerobic activity recommendations. Compliance with the step goal will be monitored through the Z11 Smart Band (Smart&Sport, Shenzhen, China) activity bracelet in the same way as the EG. For ethical reasons, the CG will have the possibility to undertake the resistance exercise intervention once the trial finalizes.

### Outcome measures

2.7

All outcome measures will be assessed at baseline and at week 12 (ie, after concluding the intervention period). Baseline assessment will be carried out during the 14 days before the beginning of the intervention and follow-up assessments will be conducted in the following 10 days from finalizing the intervention. The principal investigators ([name] and [name]) are responsible for the dataset and will only distribute it between trial investigators who are included in the funded project.

#### Primary outcome measure: muscular strength

2.7.1

The primary outcome is muscular strength because of its major clinical relevance, as it is key for a person to undertake daily activities like working, housework, and dressing among many others. Muscular strength will mainly be assessed with an electromechanical dynamometer (Dynasystem Research, Symotech, Granada, Spain)^[52–54]^ and measured in N. The primary outcome measures will be the following:

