### Sample size

2.4

The sample size was calculated for the primary outcome (ie, muscular strength) using Stata v.13 (StataCorp LP, College Station, TX). Based on the results of the meta-analysis by Strasser et al,^[23]^ a difference in the change between groups in lower limb muscle strength of at least 6.9 kg would be clinically relevant. Assuming a common standard deviation of 7.5 kg, a 90% power, an alpha error of 5%, and considering a potential dropout of 20%, we will aim at enrolling 60 participants.

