##### Upper-body muscular strength

2.7.1.1

Assessed as the average of the standardized score (*z*-score = [value−mean]/standard deviation) of 2 different exercise tests, including the sum of right and left unilateral isometric seated bench press (Fig. 1D), and the sum of right and left unilateral isometric seated row (Fig. 1F).

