##### Lower-body muscular strength

2.7.1.2

Assessed as the average of the standardized score (*z*-score = [value-mean]/standard deviation) of 2 different exercise tests, including the sum of right and left unilateral isometric knee extension in closed kinetic chain at 90° (average of the right and left knees; Fig. 1B), and the mid-thigh isometric pull test (ie, bilateral knee and hip extension; Fig. 2A).

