##### Overall muscular strength

2.7.1.3

Standardized score computed as the average of the normalized score (*z*-score = [value-mean]/standard deviation) of all the above-mentioned upper- and lower-body exercise tests (Fig. 1).

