### Statistical analysis

2.9

The distribution of the main study variables will be assessed through histogram and Q-Q plots. Descriptive characteristics will be presented using the mean and standard deviation for normally distributed quantitative variables, the median and interquartile range for non-normally distributed quantitative variables, and the number and frequency for categorical variables. The comparability of the groups will be checked at baseline and potential confounders that present baseline group differences will be included in the analyses. The between-group differences in the primary and secondary outcomes will be assessed through linear or quantile regression, as appropriate. As we aim at assessing efficacy, the primary analyses are defined as per-protocol, where participants from the exercise group will be included if their attendance to the exercise sessions is ≥75%. Sensitivity analyses will also be carried out using a minimum attendance of ≥90% and using the intention-to-treat principle. Blinded investigators ([name] and [name]) will handle all hypothesis testing. The main analyses will be conducted with Stata v.13.1 (StataCorp LP, College Station, TX). Statistical significance will be set at *P* < .05.

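### Three overlapping primary strength measures share one unadjusted P < .05; if any one suffices, the false-positive risk is roughly 7% to 11.5%, not 5%

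*Protocol article*

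**What the plan says.** Section 2.7.1 of the protocol article begins with a single concept: "The primary outcome is muscular strength because of its major clinical relevance". It continues with "The primary outcome measures will be the following" and gives three subsections:

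- **Upper-body strength (2.7.1.1)** is the mean z-score of "2 different exercise tests, including the sum of right and left unilateral isometric seated bench press" and the corresponding unilateral seated row.
- **Lower-body strength (2.7.1.2)** is the mean z-score of "2 different exercise tests, including the sum of right and left unilateral isometric knee extension in closed kinetic chain at 90" degrees and the mid-thigh pull.
- **Overall strength (2.7.1.3)** is the mean z-score "of all the above-mentioned upper- and lower-body exercise tests".

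The abstract describes the primary outcome as lower- and upper-body strength and does not mention an overall score. Section 2.9 applies linear or quantile regression to primary and secondary outcomes alike, with one threshold: "Statistical significance will be set at *P* < .05". Section 2.4 calculates the sample size for one comparison, lower-limb strength, with "an alpha error of 5" per cent.

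**The concern.** The sample size is justified by one test at 5%, but the outcome section sets up three tests under the primary label, each facing the same .05. No lead measure is designated among them. The third measure adds no new data, because it is the average of the first two, yet it gives another opportunity to reach significance. A report could therefore present whichever of the three crosses the threshold as the primary result. The 5% in section 2.4 would then no longer describe the error rate of the trial's main claim. A reader also cannot tell from the article which result decides the trial: the abstract points to two measures, section 2.7.1 to three, and section 2.4 to one.

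**Working it through.** **1. Reproduce the stated sample size.** Inputs from section 2.4: difference 6.9 kg, SD 7.5 kg, power 90%, alpha 5% (two-sided assumed), dropout 20%. Equal arms are assumed.

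n per arm = 2 × [7.5 × (1.960 + 1.282) / 6.9]² = 24.83, so 25 per arm and 50 in total. Adding 20% gives 50 × 1.2 = 60, the stated figure. This confirms that 60 comes from a single comparison at the full 5%, with nothing set aside for further primary tests.

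**2. Show the overlap.** Let upper = (z1 + z2)/2 and lower = (z3 + z4)/2. Then overall = (z1 + z2 + z3 + z4)/4 = (upper + lower)/2.

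**3. Chance of at least one false positive.** Let U and L be the standardised test statistics for upper and lower, with correlation r under no effect. If the two composites have equal variance (an assumption), the statistic for overall is O = (U + L)/√(2 + 2r). Each is tested two-sided at .05. Simulation with 3 million draws of (U, L) gives:

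| Assumed r | P(any of the three \|z\| > 1.96) | Multiple of 5% |
|---|---|---|
| 0 | 11.5% | 2.3 |
| 0.3 | 10.5% | 2.1 |
| 0.5 | 9.7% | 1.9 |
| 0.7 | 8.6% | 1.7 |
| 0.8 | 7.9% | 1.6 |
| 0.9 | 7.1% | 1.4 |

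These are two-sided rates. False claims of benefit alone run from 3.6% (r = 0.9) to 5.8% (r = 0), against a nominal 2.5%.

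**4. What the remedies do.** A fixed sequence keeps the family-wise error at 5% and leaves the first test at the full .05. A Bonferroni split (.05/3 each) gives a family-wise error of 2.5% to 4.1% over r = 0.9 to 0, but it costs power. With 60 enrolled and 20% lost, 60 × 0.8 = 48 remain, or 24 per arm. The t-test power for the 6.9 kg difference at that size is 87.7% at .05 and 75.6% at .05/3. The 87.7% is a recalculation after dropout; the planned power is 90%. Under Bonferroni, 90% power would need 32 per arm (normal approximation), which is 64/0.8 = 80 enrolled.

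**The case against.** The strongest reply is that a multiplicity rule normally belongs in the analysis plan, which is not shown, so silence here proves nothing. Section 2.9 also never says that each measure is sufficient on its own for a positive trial. If all three had to succeed, or if overall strength were meant as the single summary, there would be no inflation. This stands in part. The any-one-suffices reading is an assumption, and the size must be conditional on it. But the article does more than stay silent. It lists three primary measures, sets one flat threshold and powers one comparison, and these do not fit together. If all three were required, the error would stay within 5%, but power for the joint claim would be unplanned, since section 2.4 covers lower-limb strength only.

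Some stronger readings are tempting but are not supported:

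- **A flat doubling, or 14.3%.** A reader might infer either. The 14.3% is for three independent tests (1 − 0.95³), which these are not. Doubling holds only at low to moderate correlation, and at r = 0.9 the figure is 7.1%.
- **Further inflation from the three analysis sets.** A reader might count the ≥75% attendance, ≥90% attendance and intention-to-treat analyses as more primary tests. Section 2.9 makes the first primary and labels the other two sensitivity analyses.
- **Lower-body strength as the exact quantity that was powered.** Section 2.4 is in kg and section 2.7.1.2 defines a z-score. The body region is the same, but the quantity is not. Overall strength fits the singular aim at the end of the Introduction at least as well.

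**Conclusion.** The point holds in conditional form. Three primary measures, one of them the average of the other two, share an unadjusted .05, while the sample size assumes one comparison at 5%. If significance on any one counts as a positive primary result, the chance of at least one false positive is roughly 7% to 11.5%. It is 8.6% to 10.5% for correlations of 0.7 to 0.3. Every value in the range exceeds 5%.

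This rests on four assumptions: the any-one reading, which the text neither states nor excludes; the correlation, which the documents do not give; equal variances of the two composites; and normal test statistics. The first is decisive for whether there is inflation at all. The problem is cheap to remove and concerns the trial's main claim.

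**What to change.** Before any unblinded analysis, issue a dated amendment to the protocol and registration that:

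1. Names one lead primary measure. Lower-body strength is one option, because it is the body region behind the sample size; the amendment should acknowledge the change from kg to a z-score. Overall strength is another, because it matches the single primary aim.
2. Tests the other two in a stated fixed order, each at two-sided .05 and only while the preceding test is significant.
3. Brings the abstract and sections 2.4, 2.7.1 and 2.9 into line with that choice.

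The outcomes in section 2.7.2 are already labelled secondary and need no change on this point.

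**Cost.** No extra participants are needed, and the lead measure keeps the full .05. The work is a short paragraph, but it must be dated and reconciled with the registration of August 1, 2019, which preceded enrolment. The real price is that the second and third measures can be claimed only if those before them succeed: a non-significant lead result blocks any confirmatory claim on the other two, however strong they look. The order should therefore be chosen deliberately and without sight of results by group.

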##### Upper-body muscular strength

2.7.1.1

Assessed as the average of the standardized score (*z*-score = [value−mean]/standard deviation) of 2 different exercise tests, including the sum of right and left unilateral isometric seated bench press (Fig. 1D), and the sum of right and left unilateral isometric seated row (Fig. 1F).

**Figure 1 F1:**
[figure not shown]
Assessment muscular strength (A) mid-thigh isometric pull test and upper-body muscular strength, (B) unilateral isometric knee extension in closed kinetic chain at 90°, (C) bilateral isometric seated bench press, (D) unilateral isometric seated bench press, (E) bilateral isometric seated row, (F) unilateral isometric seated row.

##### Lower-body muscular strength

2.7.1.2

Assessed as the average of the standardized score (*z*-score = [value-mean]/standard deviation) of 2 different exercise tests, including the sum of right and left unilateral isometric knee extension in closed kinetic chain at 90° (average of the right and left knees; Fig. 1B), and the mid-thigh isometric pull test (ie, bilateral knee and hip extension; Fig. 2A).

##### Overall muscular strength

2.7.1.3

Standardized score computed as the average of the normalized score (*z*-score = [value-mean]/standard deviation) of all the above-mentioned upper- and lower-body exercise tests (Fig. 1).

#### Secondary outcomes

2.7.2

##### Other muscular strength variables

2.7.2.1

Bilateral isometric seated bench press (Fig. 1C).Isometric seated bench press bilateral deficit [bilateral deficit = (100 × bilateral/(right unilateral + left unilateral)) − 100].Bilateral isometric seated row (Fig. 1E).Isometric seated row bilateral deficit [bilateral deficit = (100 × bilateral/(right unilateral + left unilateral)) − 100].Handgrip strength (of the right and left sides) assessed with a digital dynamometer (Model T.K.K.540; Takei Scientific Instruments Co, Ltd, Niigata, Japan). Within each side, the highest score of 2 trials will be considered for the analyses.The difference between right unilateral and left unilateral handgrip strength, assessed with a digital dynamometer (Model T.K.K.540; Takei Scientific Instruments Co, Ltd).

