### Setting and eligibility criteria

2.2

Participants have been recruited through local associations and advertisements in local newspapers, radio, and social media including social networks, and through referral from clinical oncologists from the Torrecárdenas University Hospital. Eligible participants are voluntary women aged 18 to 65 who have undergone breast cancer surgery and have finished core treatments (ie, chemotherapy and/or radiotherapy) in the past 5 years. The exclusion criteria are defined as follows:

(1)presenting with metastatic breast cancer,(2)awaiting breast reconstruction in the following 6 months,(3)presenting with any pathology that might prevent participants from exercising (ie, decompensated heart failure, unstable ischemic heart disease, severe untreated high blood pressure, moderate-severe valvopathies, aortic aneurysm, moderate-severe chronic obstructive pulmonary disease, pulmonary hypertension, chronic respiratory insufficiency), and(4)regularly performing >300 minutes per week of structured exercise. This study has been reviewed and approved by the Ethics Committee of the Torrecárdenas University Hospital, Almería, Spain (ref: Ejercicio-CáncerUAL[98/2019]), on July 31, 2019.

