### Randomization, treatment allocation, and blinding

2.5

After baseline assessment, each participant will be randomized to either an experimental group (EG) or a waiting-list control group (CG). Before participant's recruitment, a blinded investigator ([name]) created a computer-generated simple randomization sequence, to allocate participants in either group. Individual allocations were held in sealed, opaque, and consecutively numbered envelopes. A member of the staff not involved in the trial assessment or interventions will open the envelopes in front of participants and assign them to the groups.

The data analysts and the primary outcome assessors will be blinded to the participant allocation. However, due to the nature of the intervention (ie, supervised resistance exercise), the participants will be aware of the group they are allocated to.

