##### Arm volume and lymphedema

2.7.2.10

Arm volume and lymphedema will be evaluated by measuring the perimeter of the arm at different points that will be 6 cm apart, to estimate the volume of both arms using the following expression^[75]^:
 

where n = number of segments, *L* = length of each segment, and *C*_*i*_ and *C*_*i*−1_ = circumference at each end of the segment. Subsequently, both volumes will be compared, and the presence of lymphedema will be considered when the volume of the affected arm exceeds the volume of the non-affected arm by 3-10%.^[76–78]^

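### The secondary handgrip difference is defined by right and left body side, not by affected and non-affected arm, so it would understate any effect specific to the operated arm

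*Protocol article*

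**What the plan says.** Among the secondary strength variables, section 2.7.2.1 lists "Handgrip strength (of the right and left sides) assessed with a digital dynamometer" and, as a separate variable, "The difference between right unilateral and left unilateral handgrip strength". Both are labelled by body side. No formula, order or absolute value is given for the difference, although the two bilateral-deficit variables in the same list do have formulas.

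Section 2.7.2.10 uses a different label for arm volume. There, lymphedema is judged by how far "the volume of the affected arm exceeds the volume of the non-affected arm", so the affected side has to be known for that outcome.

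Section 2.2 admits women who "have undergone breast cancer surgery and have finished core treatments", without restriction to right, left or one-sided surgery. Section 2.5 describes simple randomization and names no stratification by side. Section 2.9 analyses secondary outcomes by linear or quantile regression and names no term for the affected side.

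**The concern.** In a trial population in which every woman has had breast surgery, the arm contrast with a natural interpretation is operated against non-operated. Right against left is that contrast for a woman treated on the right and its reverse for a woman treated on the left. Averaged over both kinds of patient, a signed right-left difference sets one against the other. A result near zero could then be reported as no change in asymmetry even if the operated arm had gained relative to the other. Handgrip shown for the right hand and the left hand has a milder form of the same problem: each hand's mean pools operated and non-operated arms, so neither describes the operated arm.

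**Working it through.** The plan gives no figure for this outcome, so there is nothing to reproduce. The check is algebra, followed by an illustration.

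**Inputs**

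- Definition by right and left, sign not stated: section 2.7.2.1.
- Sample of 60 with 20% dropout: section 2.4. This gives 60 × 0.8 = 48, or 24 per arm if the arms are equal.
- p, the share of right-sided patients among women with one-sided surgery: not given. Assumed range 0.50 to 0.70, taken as equal in both arms, as simple randomization gives on average.
- d, the treatment effect on the change in affected minus non-affected handgrip: not given.

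**Signed difference.** For a right-sided patient, right minus left equals affected minus non-affected, so the effect is +d. For a left-sided patient it is −d. The mean effect is p·d + (1−p)·(−d) = (2p−1)·d.

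| p | share of d kept |
|---|---|
| 0.50 | 0% |
| 0.55 | 10% |
| 0.60 | 20% |
| 0.70 | 40% |
| 1.00 | 100% |

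Below 0.50 the sign reverses; p = 0.40 gives −20%. Affected minus non-affected keeps 100% at every p.

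**Right and left hands separately.** Let c be the effect shared by both arms and d the extra effect in the operated arm. The right-hand effect is c + p·d and the left-hand effect is c + (1−p)·d. At p = 0.50 both are c + 0.5d; at p = 0.60 they are c + 0.6d and c + 0.4d. Neither extra term changes sign, and c is kept in full. This is dilution, not cancellation.

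**Illustration.** Simulation of 20,000 trials with 24 per arm and a two-sample t test on change. All of the following are assumed and do not come from the article: d = 2 kg, SD of change 2.5 kg, and a baseline affected-minus-non-affected gap with mean −3 kg and SD 3 kg. Cells show the mean effect, with the rejection rate at the 5% level in brackets.

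| p | affected minus non-affected | signed right minus left | absolute difference |
|---|---|---|---|
| 0.50 | 2.0 kg (0.77) | 0.00 kg (0.05) | −0.78 kg (0.21) |
| 0.55 | 2.0 kg (0.77) | 0.20 kg (0.06) | −0.78 kg (0.21) |
| 0.60 | 2.0 kg (0.77) | 0.40 kg (0.08) | −0.78 kg (0.20) |
| 0.70 | 2.0 kg (0.78) | 0.80 kg (0.16) | −0.78 kg (0.20) |

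A negative value in the last column means that the asymmetry shrank. The absolute difference does not depend on p, but it loses much of the effect. It also cannot tell which arm was weaker.

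**Primary outcomes.** Section 2.7.1.1 uses "the sum of right and left unilateral isometric seated bench press" and the corresponding sum for the row. Section 2.7.1.2 uses a right-left combination for knee extension and a bilateral pull. Right plus left equals affected plus non-affected, so side labelling does not touch these composites.

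**The case against.** Most of the opposing case concerns how far the point reaches, and several parts of it stand.

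- **Sign.** A reader might infer that the outcome is right minus left and that gains in the operated arm therefore cancel. The article says only that it is a difference. An absolute asymmetry is an available reading, and under it nothing cancels between right- and left-sided patients. Even on the signed reading, complete cancellation needs an even split of sides.
- **Purpose.** A reader might infer that the variable exists to follow the operated arm and so fails at its own aim. The article does not say so. Section 2.7.1 justifies strength in general by daily activities.
- **Side-specific effect.** The article gives no handgrip deficit by operated side and no expected effect specific to that arm. Section 2.6.1 describes four main resistance exercises, all bilateral. If both arms gain alike, d is near zero and recoding recovers little.
- **Analysis plan.** A sign convention or a rule for bilateral surgery may stand in an analysis plan that is not shown, and its absence here is not the point. The point is that the outcome as stated is defined by body side.
- **Wider remedies.** It is tempting to ask for adjustment for hand dominance and for the same coding of shoulder flexion. The article does not show that dominance is recorded, and section 2.7.2.3 states no side coding, so neither request has support.

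What remains is that both handgrip variables are labelled by body side, nothing elsewhere in the article recodes them, and neither the signed nor the absolute reading isolates the operated arm.

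**Conclusion.** The point holds as a limited weakness in the definition of secondary handgrip variables. On the signed reading, the loss is exactly the factor (2p−1) if p is the same in both arms: nothing is kept at p = 0.50, 20% at 0.60 and 40% at 0.70. On the absolute reading, the effect is diluted to an extent that depends on the baseline gap and the spread of change, for which the article gives no values. Separate right and left handgrip dilute an arm-specific effect and keep a shared one in full.

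The size in this trial cannot be stated, because p, d and even the existence of an arm-specific effect are assumptions. The primary composites do not depend on side labelling. The change is worth making because the affected side is already needed for the lymphedema outcome and the present label gains nothing from ignoring it.

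**What to change.** In section 2.7.2.1, define the difference as affected minus non-affected handgrip, signed, and report handgrip by affected and non-affected arm in place of, or beside, right and left. Adjust the between-group comparison for the baseline value of the same variable. State that women with bilateral surgery are left out of the side contrast only and stay in all other analyses.

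Both hands are already measured and the affected side is already required by section 2.7.2.10, so the cost is recoding. The downside is a slightly smaller sample for the side contrast, by the number of women with bilateral surgery, which the article does not give.
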